Clinical Study Protocol (Study Title) Study Identifier

This document is the xx Clinical Protocol template for IIT (Investigator initiated Trials) studies. XX strongly recommends using this template to develop clinical research protocols for trials testing an investigational medicinal product (IMP) or a medical device (MD) to be submitted to Swiss authorities.

This template is suitable for studies:

- involving IIT,
- performed in Switzerland, respectively where the Sponsor-Investigator is located in Switzerland
- where the study question does relate to the use of drug(s) or medical device effect(s),
- where the Swiss law on therapeutic products (HMG/LPTh and Federal Act on Medicinal Products and Medical Devices) applies,
- where the Swiss law on human research (LHR) and its applicable ordinance KlinV/OClin applies,
- that are interventional*

*health related interventional studies include research in preventive, diagnostic, therapeutic, palliative or rehabilitation activities that are examined in the context of a clinical trial.

The current template is based on:

- [AGEK – CT CER](http://www.swissethics.ch/templates.html) / [Swissmedic](http://www.swissmedic.ch/bewilligungen/00089/00282/index.html?lang=de) guidelines: “Studienprotokolle von klinischen‚ Investigator-initiated’ Studien/Versuchen / Exigences des protocoles d’études/d’essais cliniques initiés par l’investigateur” dated 24.02.2009,
- new law on human research ([LHR](http://www.bag.admin.ch/themen/medizin/00701/00702/07558/index.html?lang=de)) and its applicable ordinance [KlinV/OClin](http://www.bag.admin.ch/themen/medizin/00701/00702/12310/index.html?lang=de)
- the [SPIRIT statement](http://www.spirit-statement.org) and
- [ICH-GCP E6](http://www.ich.org/fileadmin/Public_Web_Site/ICH_Products/Guidelines/Efficacy/E6_R1/Step4/E6_R1__Guideline.pdf), section 6
- [EN ISO14155:2011](https://www.iso.org/obp/ui/#iso:std:iso:14155:ed-2:v1:en): Annex A
- Swiss clinical trial registration portal ([www.kofam.ch](http://www.kofam.ch)) - check name and link

This template attempts to provide a general format applicable to all clinical trials evaluating an investigational product (drugs or medical devices).

Note that *instructions* are indicated in *blue italics* and they need be deleted (or alternatively may be formatted as “hidden Text” that will not show in printing).

10.1.2 Reporting of serious adverse events (SAE) and other safety related events 32

10.1.3 Follow up of (Serious) Adverse Events 32

11. STATISTICAL METHODS 33

11.1 Hypothesis 33

11.2 Determination of Sample Size 33

11.3 Statistical criteria of termination of trial 33

11.4 Planned Analyses 33

11.4.1 Datasets to be analysed, analysis populations 33

11.4.2 Primary Analysis 33

11.4.3 Secondary Analyses 34

11.4.4 Interim analyses 34

11.4.5 Safety analysis 34

11.4.6 Deviation(s) from the original statistical plan 34

11.5 Handling of missing data and drop-outs 34

12. QUALITY ASSURANCE AND CONTROL 35

12.1 Data handling and record keeping / archiving 35

12.1.1 Case Report Forms 35

12.1.2 Specification of source documents 35

12.1.3 Record keeping / archiving 35

12.2 Data management 35

12.2.1 Data Management System 35

12.2.2 Data security, access and back-up 36

12.2.3 Analysis and archiving 36

12.2.4 Electronic and central data validation 36

12.3 Monitoring 36

12.4 Audits and Inspections 36

12.5 Confidentiality, Data Protection 36

12.6 Storage of biological material and related health data 36

13. PUBLICATION AND DISSEMINATION POLICY 37

14. FUNDING AND SUPPORT 38

14.1 Funding 38

14.2 Other Support 38

15. INSURANCE 38

16. REFERENCES 39

17. APPENDICES 41

Study synopsis

| Sponsor / Sponsor-Investigator | Swiss Paraplegic Centre Nottwil / [name] |
| --- | --- |
| Study Title: | Influence of caffeine on heart rate variability and performance in paraplegic and tetraplegic subjects compared to able-bodied subjects: a pilot study |
| Short Title / Study ID: | HRV and caffeine in disabled and able-bodied subjects. |
| Protocol Version and Date: | Version No. 2, 15.07.2014 |
| Trial registration: | ClinicalTrials.gov NCT02083328 |
| Study category and Rationale | Low Risk Clinical Trial (Category A) (Supplementation with caffeine corresponds to international guidelines) |
| Clinical Phase: | N/A |
| Background and Rationale: | The aim is to investigate the influence of caffeine on heart rate variability and on performance in a 3 min exercise test in different population groups (able-bodied, paraplegic and tetraplegic subjects). |
| Objective(s): | In general, we are interested in the differences between the heart rate variability before and after caffeine supplementation and if exercise performance is enhanced using this type of supplementation. Another objective is to see whether there are differences between abled-bodied and disabled subjects as subjects with spinal cord injury have an impairment of the autonomic nervous system. |
| Outcome(s): | Primary outcome parameters are differences in heart rate variability and power output in the exercise performance test between caffeine and placebo trial. Secondary outcome parameters are epinephrine and norepinephrine concentration before and after caffeine supplementation, heart rate, tidal volume, lactate concentration before and after the exercise testing, as well as rating of perceived exertion after the exercise performance test. |
| Study design: | Randomised, double-blind, placebo controlled trial (RCT); pilot study |
| Inclusion / Exclusion criteria: | Inclusion: healthy, non-smoker, minimal 3x45 min physical activity per week, tetraplegic (C5 to C7) or paraplegic (sub Th8), AIS A, termination of first rehabilitation and more than 6 months after trauma.  Exclusion: drugs or supplements which influence heart rate variability, diabetes |
| Measurements and procedures: | Heart rate variability (HRV) is measured using a Polar heart rate monitor. After a 10min rest, HRV is measured during a 5 min phase in supine position and afterwards during a 6 min time period in sitting position. These measurements are conducted before the ingestion of the supplement, before the exercise performance test and after the exercise performance test.  Epinephrine and norepinephrine concentrations are measured before supplementation and one hour after supplementation (venous blood withdrawal).  Resting tidal volume is measured during the measurements of HRV.  Power output during the 3 min exercise performance test is analysed.  Lactate concentration is measured before and after the exercise performance testing taking a capillary blood sample.  Blood pressure is measured immediately before every HRV measurement.  Rate of perceived exertion is measured after the warm up and after the exercise performance test. |
| Study Product / Intervention: | Caffeine: 6 mg/kg body mass dosage, supplement will be ingested 1 hour before the exercise performance test respectively 45 min before the HRV measurement. |
| Control Intervention (if applicable): | Placebo (mannitol) |
| Number of Participants with Rationale: | 30 participants in total (10 per each group of able-bodied, tetraplegic and paraplegic subjects): this study is a pilot study thus no power analysis was performed. |
| Study Duration: | 20 months |
| Study Schedule: | 01. May 2014: start of data collection  31. December 2015: end of data collection |
| Investigator(s): | [name]  Sports Medicine, Swiss Paraplegic Centre, [name], [contact], [contact] |
| Study Centre(s): | Single-center study: Swiss Paraplegic Centre Nottwil |
| Statistical Considerations: | For analysing the differences pre and post ingestion of caffeine within a subject, a Wilcoxon test will be used.  The correlation between HRV and performance under caffeine treatment will be evaluated with the Spearman’s rank correlation coefficient. |
| GCP Statement: | This study will be conducted in compliance with the protocol, the current version of the Declaration of Helsinki, the ICH-GCP or ISO EN 14155 (as far as applicable) as well as all national legal and regulatory requirements. |

study summary in local language can be provided here (German)

Die Herzfrequenzvariabilität (HRV) beschreibt die Varianz der Zeitintervalle zwischen den einzelnen Herzschlägen. Sie ist ein Parameter zur Bestimmung der Funktion des Sympathikus und Parasympathikus des autonomen Nervensystems. Diese beiden Komponenten haben antagonistische Aufgaben bei der Regulation der viszeralen Funktion des Körpers. Während der Sympathikus eine eher anregende Wirkung hat, hemmt der Parasympathikus.

Aus der Analyse der HRV resultieren zwei Komponenten, welche den zwei Systemen zugeordnet werden können. Die low frequency (LF) repräsentiert den Sympathikus während die high frequency (HF) dem Parasympathikus zugeordnet wird.

Je mehr also zum Beispiel der Sympathikus aktiviert ist, desto grösser ist der Anteil des LF- im Vergleich zur HF-Komponente. Mit der Analyse der HRV lassen sich so Aussagen über die sympathische-parasympathische Balance machen.

Bei querschnittgelähmten Personen ist durch die Verletzung des Rückenmarks auch das autonome Nervensystem betroffen. Davon ist, aufgrund seiner Austritthöhe entlang der Wirbelsäule bis ca. zum 6. Brustwirbel, nur der sympathische Anteil betroffen. Der Parasympathikus dagegen tritt auf Hirnstamm-Höhe aus und ist so nicht direkt von der Unterbrechung der Rückenmarks betroffen.

Je höher die Läsion, desto höher ist die Beeinträchtigung des Sympathikus. Dies hat folglich auch Auswirkungen auf die HRV: Das sympathische-parasympathische Gleichgewicht ist aufgrund des Sympathikus-Ausfalls gestört. So haben HRV-Messungen bei Tetraplegikern ergeben, dass die LF-Komponente meist nicht mehr vorhanden ist und gleichzeitig die HF-Komponente erniedrigt ist. Bei Paraplegikern wurde zwar die LF und die HF gemessen, jedoch waren beide Komponenten abgeschwächt im Vergleich zu gesunden Referenzpersonen.

Welche Auswirkungen ein Stimulanz des autonomen Nervensystems auf die HRV bei Querschnittgelähmten hat, wurde bisher noch nicht untersucht. Wir nehmen an, dass eine Supplementierung mit Coffein messbare Effekte auf die HRV bei dieser Patientengruppe hat. Bei gesunden Referenzpersonen wurde durch eine Supplementierung mit Coffein eine Leistungsverbesserung im anaeroben hochintensiven Bereich beobachtet. Ob dieser Effekt auch bei Querschnittgelähmten auftritt, ist noch nicht abschliessend geklärt.

Mit unserer Studie untersuchen wir den Effekt einer Coffeinsupplementierung auf die HRV und die Leistungsfähigkeit bei querschnittgelähmten Probanden im Vergleich zu gesunden Referenzpersonen.

Dabei vergleichen wir die HRV-Werte vor und nach Einnahme von Coffein innerhalb und zwischen den Gruppen (Tetraplegiker, Paraplegiker, Referenzpersonen) und messen den Effekt auf die Leistungsfähigkeit durch eine Coffeinsupplementierung.

Durch diese Studie möchten wir mehr Grundlagenwissen im Bereich der HRV-Messung bei Querschnittgelähmten erlangen, um so die Möglichkeit der Verwendung einer solchen Messung im Bereich der Klassifizierung der Läsionen zu untersuchen oder beim Einsatz der Trainingsgestaltung bzw. der Vorbeugung von Übertraining. Weiter erhoffen wir uns durch die Studie mehr Kenntnisse über die Sinnhaftigkeit einer Coffeinsupplementierung bei querschnittgelähmten Athleten.

Die geplante Studie soll neue Erkenntnisse erschliessen und so einen Schritt zum besseren Verständnis der Funktionsweise der HRV bei Querschnittgelähmten beitragen.

Abbreviations

| AE | Adverse Event |
| --- | --- |
| ANS  CA | Autonomic Nervous System  Competent Authority (e.g. Swissmedic) |
| CEC | Competent Ethics Committee |
| CRF | Case Report Form |
| eCRF | Electronic Case Report Form |
| CTCAE | Common terminology criteria for adverse events |
| DSUR | Development safety update report |
| GCP | Good Clinical Practice |
| IB | Investigator’s Brochure |
| Ho | Null hypothesis |
| H1 | Alternative hypothesis |
| HFG | Humanforschungsgesetz (Law on human research) |
| HMG | Heilmittelgesetz |
| HRV  IMP | Heart rate variability  Investigational Medicinal Product |
| IIT | Investigator-initiated Trial |
| ISO | International Organisation for Standardisation |
| ITT | Intention to treat |
| KlinV | Verordnung über klinische Versuche in der Humanforschung |
| LHR | Law on human research |
| LPTh | Loi sur les produits thérapeutiques |
| LRH | Loi fédérale relative à la recherche sur l’être humain |
| MD | Medical Device |
| OClin | Ordonnance sur les essais cliniques dans le cadre de la recherche sur l'être humain |
| PI  RPE | Principal Investigator  Rate of perceived exertion |
| SDV  SCI | Source Data Verification  Spinal Cord Injury |
| SOP | Standard Operating Procedure |
| SPC | Summary of product characteristics |
| SUSAR | Suspected Unexpected Serious Adverse Reaction |
| TMF | Trial Master File |

Study schedule

| Study Periods | Recruitment | Screening and Familiarization | Intervention Period | |
| --- | --- | --- | --- | --- |
| Visit | 1 | 2 | 3 | 4 |
| Time | individual | individual | 09:00 | 09:00 |
| Patient Information and Informed Consent | X | - | - | - |
| Subject Group | X | X | X | X |
| Medical History | X | - | - | - |
| In- /Exclusion Criteria | X | - | - | - |
| Checklist | - | - | X | X |
| VO_2max_ Test | - | X | - | - |
| Vital Signs | - | - | X | X |
| Laboratory Tests (Catecholamine) | - | - | X | X |
| Randomisation | X | - | - | - |
| HRV Measurement | - | - | X | X |
| 3 min Performance Test | - | X | X | X |
| Tidal Volume Measurement | - | - | X | X |
| Venous Blood Sample | - | - | X | X |
| Capillary Blood Sample | - | - | X | X |
| Blood Glucose Level | X | - | - | - |
| Blood Pressure Measurement | - | - | X | X |
| Ingestion of Caffeine or Placebo | - | - | X | X |
| Adverse Events | - | - | X | X |

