# STUDY DESIGN

## General study design and justification of design

Our study will be conducted in a placebo-controlled, double-blind and randomised study protocol. In total every subject visits the Sport Medicine for four times whereas every visit takes 2 hours expect for the first one where only 30min are needed. Every subject has to undergo three test sessions at the Institute of Sports Medicine in Nottwil. Before these three sessions the subject will visit the Institute of Sports Medicine in Nottwil for recruitment issues which involves study informed consent and a health questionnaire with specific questions about diseases and family health history including a measurement of blood glucose level.

Then at the screening, the subjects have to perform a maximal exercise test (ramp protocol at the arm crank ergometer) to measure maximal oxygen uptake, maximal heart rate and maximal power output. After a little break, subjects have to perform a familiarization trial at the arm crank ergometer (Angio V2, Lode, Groningen, Netherlands). They have to perform exactly the same test as they have to perform later in the two test sessions.

Minimum two days and maximum two weeks later the subjects visit the Sports Medicine Nottwil for the first test session. At first, they have to answer some specific questions about sleep, recent training, recent nutritional intake and the actual health condition. Afterwards, they have to lie down for a 10 min rest where after 9 min blood pressure will be measured. HRV will be measured during 5 min the supine position and 6 min in the sitting position by means of a heart rate monitor. Paced breathing (15x/min) [12] is mandatory and will be paced through a metronome. During the HRV measurement also tidal volume will be measured. As the first HRV measurement session is finished, a venous blood withdrawal will be taken to measure catecholamine concentrations. Then, when all these measurements are completed, a supplement (either caffeine or the placebo) will be ingested in gelatine capsules. After the ingestion of these capsules, the subject has a 40 min break where they can read something or just relax. During these 40 min physical activity or the ingestion of any nutrition is prohibited.

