### Other methods of minimising bias

After the recruitment visit the subjects will visit the Institute of Sports Medicine in Nottwil performing the 3 min performance test for familiarization purposes.

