# STATISTICAL METHODS

This study is a pilot-study with a small sample size. Therefore, normal distribution of the data cannot be assumed. Descriptive statistics, i.e. median, 25/75% quartiles, 95% confidence intervals and range, will be used. A p-value of < 0.05 will be considered significant, even though multiple hypotheses will be tested.

The treatment period (i.e. sequence of placebo and caffeine treatment) will not be included into the statistical analysis, because the wash-out period (48h) is considered more than long enough to prevent any carry-over effect. Furthermore, the period effect is considered to be negligible, because study participants will undergo a training session before the collection of data in order to avoid any learning effect.

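### Section 11's reason for ignoring period covers power output but not the primary HRV change, because the training session rehearses only the 3 min test

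*Protocol*

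**What the plan says.** Section 11 (Statistical Methods) sets the rule: "The treatment period (i.e. sequence of placebo and caffeine treatment) will not be included into the statistical analysis". It gives the wash-out as the reason against carry-over. Against a period effect it gives one reason: "the period effect is considered to be negligible, because study participants will undergo a training session before the collection of data". No outcome is excepted. Sections 11.1 and 11.4.2 then name two primary hypotheses, power output and change in HRV from baseline. Each is tested by a signed-rank test within each of the three groups, with no period term.

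The training session is visit 2. Section 6.2.3 describes it as "performing the 3 min performance test for familiarization purposes", and sections 6.1 and 9.3 add only a VO2max test. The study schedule agrees:
- exercise test: "3 min Performance Test | - | X | X | X"
- HRV: "HRV Measurement | - | - | X | X"
- tidal volume: "Tidal Volume Measurement | - | - | X | X"

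Section 6.1 describes the HRV procedure as a 10 min rest, 5 min supine and 6 min sitting, with tidal volume measured throughout. Breathing is at 15 per minute, which "is mandatory and will be paced through a metronome".

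Sections 6.2.1 and 7.3 assign order by lot, half of all subjects to each order. Neither says that the halves are balanced within the three groups.

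**The concern.** The justification and the schedule do not match for one of the two primary outcomes. A man has practised the 3 min test once before session 1. He has not practised the resting, paced-breathing sequence. The pre-dose recording of session 1 is his first in the study, whereas the pre-dose recording of session 2 follows three earlier ones.

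If men settle into the procedure between their first and second recording, the session 1 change contains that settling and the session 2 change does not. Subtracting the same session's baseline does not remove such a difference. With no period term, it goes into the spread of the caffeine-placebo differences. If the two orders are unequal within a group, it also goes into their centre. With about ten men per group there is little room for either.

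**Working it through.** The documents give no figure for an HRV period effect, so there is none to reproduce. The check has two parts.

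**1. Does the stated reason reach HRV?** Section 11 rests on the training session. The schedule and sections 6.1, 6.2.3 and 9.3 all limit that session to the VO2max and 3 min tests. The reason therefore reaches power output only. It does not reach catecholamines either, since venous sampling also starts at visit 3.

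**2. What could it cost?**

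Inputs from the protocol: at least 10 complete data sets per group (11.4.1), two-sided hypotheses (11.1), significance at 0.05 (11), the signed-rank test (11.4.2), and order 1:1 by lot overall (6.2.1).

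Assumptions: P is the session 1 minus session 2 difference in within-session HRV change, in SDs of the within-man caffeine-placebo difference. It is set to 0, 0.25, 0.5 and 1. The true caffeine effect is 1 SD, and differences are normal.

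The expected difference is effect + P for a man who takes caffeine first and effect - P for a man who takes placebo first. Hence:
- bias = P x (n1 - n2)/n, where n1 men take caffeine first. This gives 0 at 5:5, 0.2 x P at 6:4, 0.4 x P at 7:3 and 0.6 x P at 8:2.
- at 5:5 the SD of the differences grows by sqrt(1 + P^2): sqrt(1.0625) = 1.03, sqrt(1.25) = 1.12 and sqrt(2) = 1.41.

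Simulated signed-rank test, n = 10, 40,000 runs per setting:

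| P | Power, 5:5 | Type I error, 5:5 | Type I error, 7:3 | Type I error, 8:2 |
|---|---|---|---|---|
| 0 | 0.79 | 0.047 | 0.047 | 0.051 |
| 0.25 | 0.76 | 0.042 | 0.054 | 0.065 |
| 0.5 | 0.69 | 0.030 | 0.062 | 0.102 |
| 1 | 0.44 | 0.006 | 0.061 | 0.190 |

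How likely is an unequal split in a group of ten?
- Independent lots (binomial): exactly 5:5 in 24.6%, 7:3 or worse in 34.4%.
- Exactly 15 of 30 in each order overall (hypergeometric): 5:5 in 30.0%, 7:3 or worse in 24.5%. At least one of the three groups departs from 5:5 with probability 89.7%.

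These figures use the contrast in section 11.1. Section 5.1 words the HRV outcome as before versus after caffeine, with no placebo term. On that wording, drift within a session would not cancel even with balanced order.

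**The case against.** A reader might infer that first-exposure effects are present in the HRV contrast and bias it. The documents do not support that. No passage reports adaptation to the procedure. A shift common to both resting recordings of session 1 cancels in the change score, and only a difference in the change itself survives. Order is randomised: averaged over independent lots, the simulated type I error stays at 0.048 to 0.049 for every P, so on average the cost is power and not false positives. Each of these recordings follows a 10 min rest at a fixed breathing rate. The mask may not be new, since visit 2 measures oxygen uptake. Section 3.4 states that HRV reproduces fairly well after spinal cord injury. All of this stands and limits the point. However, section 11 does not invoke reproducibility, and the statement does not cover the able-bodied group.

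A reader might also infer that the protocol rules a period effect out, or that the HRV row of the schedule is an error. Neither is so. Section 11 only considers the effect negligible. The row agrees with every description of visit 2, and the weak text is the sentence in section 11. That this sentence is meant for both primary outcomes is a reading of its unqualified wording.

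Finally, the synopsis and section 11.2 call this a pilot without a power analysis, although section 6.2.1 gives one. The power figures therefore show scale only. The fall to 0.44 needs a session difference as large as the assumed caffeine effect. At P = 0.25 the loss is about 0.03.

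**Conclusion.** The point holds as a gap in the protocol's reasoning with a possible, unmeasured cost. The training session supports ignoring period for power output and says nothing about HRV change. If the session difference P is zero, nothing is lost. If it is not, equal orders mean lost power and no bias. Unequal orders within a group add a bias proportional to P in the split that occurs, and unequal orders are more likely than not because balance by group is not stated. The sizes rest on assumed values of P, an assumed effect of 1 SD, normal differences and ten men per group. Section 11 already fixes the omission of period and its reason, and a later analysis plan could not supply a missing rehearsal. It is worth correcting because one of two primary outcomes is affected and the remedy is cheap.

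**What to change.** Preferred: at visit 2, before the VO2max test so that exercise does not disturb it, run one unanalysed rehearsal of the HRV sequence (rest, mask, metronome at 15/min, supine, sitting). Mark it in the schedule as a rehearsal. Limit the section 11 argument to the rehearsed outcomes, and do not claim it for catecholamines. The cost is 10 + 5 + 6 = 21 min plus set-up, with the same staff and non-invasive equipment. Section 6.1 puts visit 2 at around 75 min and also allows 2 h per visit: 75 + 21 = 96 min, which leaves 24 min for set-up.

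If no rehearsal is added:
- restrict the section 11 rationale to power output;
- balance order within each of the three groups;
- add a period-adjusted HRV comparison as a sensitivity analysis, for example a rank-sum test, between the two orders, of each man's session 1 minus session 2 difference in HRV change.

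This route takes no visit time. It costs a change to the lot procedure, one extra analysis and a reworded sentence.
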